### Objectives

In this trial, we withdraw ICS in patients with T2-low asthma and obesity to determine the effects on asthma control. We hypothesize that ICS withdrawal is non-inferior to ICS continuation in patients with asthma and obesity. Additionally, this trial uses common T2-biomarkers to detect patients that become T2-high after ICS withdrawal; T2-hidden asthma.

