**Questionnaires**
**ACQ-5:** In this study the ACQ-5 will be used, consisting of five patient self-reported questions. The recall time is one week with a score range of 0 to 6 (0 = never and 6 = always). A higher score is associated with worse asthma control. The minimal clinically important difference of the ACQ is 0.5 [23].**AQLQ:** The AQLQ consists of 32 items with a 3 week recall period. The score range per question is 1 to 7 (1 = severely impaired and 7 = not impaired at all). It is used to qualify the disease-specific health-related quality of life [24–26].**MRC:** The MRC (Medical Research Council) is a dyspnea scale, as a measure of disability in patients with respiratory disabilities. It consists of one question about the shortness of breath and six possible answers. The score range per question is 0 to 5 (0 = no shortness of breath at all and 5 = too breathless to leave the house). A higher score is therefore associated with a high burden of disease [27].**FSS:** The FSS (Fatigue Severity Scale) measures fatigue severity. It has 9 items with are scored on a 7 point Likert scale. A higher score is associated with higher fatigue severity [28].

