## Sample size and statistical analysis

### Sample size calculation

The primary endpoint is the mean difference in ACQ score between the intervention period and the control period whit correction for the baseline ACQ score. This will be tested using a paired t-test for within-subjects designs, with a one-sided alpha of 0.05, a beta of 0.10, a rho of 0.5, a non-inferiority margin of 5% (0.25 ACQ points), an allowable difference (a minimal clinically important difference) of 0.5 ACQ points and a drop-out rate of 10%. The population variance $${\upsigma }_{\mathrm{e }}^{2}$$ was calculated using a real live cohort of patients in the Franciscus Gasthuis & Vlietland. This cohort included all new referrals at the outpatient clinic with a suspicion of asthma. This cohort (n = 52) was selected for having a BMI ≥ 30, blood eosinophils ≤ 0.15 cells/µl, clinically proven asthma, and no obstructive lung diseases otherwise. All patients filled in an ACQ at baseline and 6 months, after which the difference $${ACQ}_{endpoint}- {ACQ}_{baseline}$$ was calculated for every patient. This resulted in a mean of − 0.2749 with a variance 0.7847. A sample size of 120 patients was calculated using the formulae in Fig. 5.

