### Statistical analysis

Study data will be analysed according to the intention-to-treat approach. Results of the statistical analysis consist of descriptive univariable and multivariable analysis. Continuous parameters with (approximately) normal distributions will be summarized with means and SDs (or 95% CIs). Continuous primary study parameters with skewed distributions will be summarized with medians and interquartile ranges (IQR). Finally, nominal and ordinal primary study parameters will be summarized with numbers (percentages).**Primary study parameter**

The primary endpoint is defined as the difference in ACQ between the intervention period and control period relative to the baseline ACQ score. Definitions:Baseline: ACQ score at the first visit of period 1 or period 2Endpoint: ACQ at last visit of period 1 or period 2

The non-inferiority margin is 5% (i.e., 0.25 out of a maximum of 5 ACQ points). Non-inferiority will be established if the lower limit of a one-sided 95% confidence interval for the mean difference in ACQ score between the intervention period and control period is within the absolute 5% non-inferiority margin of the mean in the control arm.2.Secondary study parameter(s)

The time to first exacerbation will be tested with Kaplan–Meier curves and log-rank tests to estimate the effect over time for both patient groups. Next, Cox regression will be used to measure the treatment effect adjusted for BMI and hospital as fixed covariates.

The majority of secondary variables are continuous and will be described by descriptive compared between intervention group and control group.

The change in time of several secondary parameters will be estimated by repeated measurements analysis. Linear mixed modeling will be used for continuous variables. Generalized estimated equations for binary data with logit link function will be used for the categorical variables.3.Interim analysis

No interim analysis has been planned to prevent alpha loss. An independent Data Safety Monitoring Board (DSMB) may conduct an investigation of adverse events when ≥ 12 exacerbations may have occurred.

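### The primary non-inferiority rule leaves the sign of the ACQ contrast undefined and, on its natural reading, tests the limit that does not bound harm

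*Protocol article*

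**What the plan says.** The Objectives section sets the direction of the claim: "We hypothesize that ICS withdrawal is non-inferior to ICS continuation". The Statistical analysis section defines the endpoint: "The primary endpoint is defined as the difference in ACQ between the intervention period and control period relative to the baseline ACQ score". It then gives one decision rule: "Non-inferiority will be established if the lower limit of a one-sided 95% confidence interval for the mean difference in ACQ score" between the two periods "is within the absolute 5% non-inferiority margin of the mean in the control arm". The margin is 0.25 ACQ points.

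Under Questionnaires, the article says of the ACQ-5: "A higher score is associated with worse asthma control".

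The sample size section gives the test, "This will be tested using a paired t-test for within-subjects designs", and the error rates and correlation, "with a one-sided alpha of 0.05, a beta of 0.10, a rho of 0.5". It adds a variance of 0.7847 for the six-month ACQ change in a reference cohort, 10% drop-out and a total of 120 patients. It computes change in that cohort as endpoint minus baseline, so a positive change is a worsening.

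The article mentions no upper limit, writes no order of subtraction and gives the margin no sign.

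**The concern.** A non-inferiority claim has to exclude harm as large as the margin. If the difference is intervention minus control and a high score is bad, harm lies on the positive side and the upper limit must fall below +0.25. A one-sided interval with only a lower limit has no bound on that side. A lower-limit rule suits outcomes where higher is better, and ACQ runs the other way.

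Intervention minus control is the natural reading for three reasons: the intervention period is named first each time, the control mean is the reference for the margin, and ACQ change is kept on its original scale.

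This is the only decision rule for the primary endpoint of a trial that asks whether ICS can be safely withdrawn. Because the wording allows several incompatible tests, the choice among them could be made after the results of an open-label trial are known.

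**Working it through.** **Inputs.** From the sample size section: variance of ACQ change 0.7847, rho 0.5, one-sided alpha 0.05, power 0.90, margin 0.25, drop-out 10%, N = 120. From the Questionnaires section: higher is worse, and the minimal clinically important difference is 0.5.

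**Step 1: reproduce the planned N.**
- Variance of the within-patient difference = 2 × 0.7847 × (1 − 0.5) = 0.7847. It equals the cohort variance only because rho is 0.5.
- n = 0.7847 × (1.645 + 1.282)² / 0.25² = 107.5, so 108 completers.
- 108 / (1 − 0.10) = 120, which agrees with the article.

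This formula assumes a true difference of zero and a test that excludes harm of 0.25 at one-sided 5%.

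**Step 2: precision.** SE = √(0.7847 / 108) = 0.0852. One-sided half-width = 1.645 × 0.0852 = 0.140.

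**Step 3: chance of declaring non-inferiority.** Let d be the observed intervention-minus-control difference, taken as normal with this SE.
- *Harm-side rule*, upper limit < +0.25: passes if d < 0.25 − 0.140 = 0.110.
- *Rule as written*, lower limit within 0.25 on the harmful side: passes if d < 0.25 + 0.140 = 0.390. Reading it as the absolute lower limit below 0.25 gives the same figures at the true worsenings of 0.25 and above in the table.

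| True worsening | Harm-side rule | Rule as written |
|---|---|---|
| 0.25 | 5.0% | 95.0% |
| 0.35 | 0.2% | 68.1% |
| 0.50 | <0.01% | 9.9% |

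For the last entry: (0.390 − 0.5) / 0.0852 = −1.29, and Φ(−1.29) is about 0.099. At a true difference of zero the harm-side rule passes 90.1% of the time, which is the planned power.

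The lower limit exceeds zero once d is above 0.140. An observed worsening between 0.14 and 0.39 would therefore be statistically significant and still pass the rule as written.

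**Step 4: sensitivity, 108 completers.**
- rho 0.3: variance 2 × 0.7847 × 0.7 = 1.099, SE 0.101, passing bound about 0.42, about 20% at a true worsening of 0.5.
- rho 0.7: variance 2 × 0.7847 × 0.3 = 0.471, SE 0.066, passing bound about 0.36, about 2% at 0.5.
- All 120 patients analysed, rho 0.5: SE 0.081, passing bound 0.383, 7.4% at 0.5.

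The 95% at the margin is the same in every case, because the distance to the bound is then exactly 1.645 SE.

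**Step 5: the reversed contrast.** With control minus intervention and lower limit > −0.25, the pass rate is 5.0% at a true worsening of 0.25 and 90.1% at zero. That is the harm-side rule with its sign changed.

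**The case against.** The strongest reply is that the article never writes intervention minus control. A difference between two periods is unsigned, and with control minus intervention a lower limit above −0.25 is the correct test. The sign may be fixed in the sample size formulae (Fig. 5, not shown), the full protocol or an analysis plan. The hypothesis, the alpha and the reproducible sample size all show that a proper test was intended, so this may be a slip of wording.

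Much of this stands. It is not proven that the wrong limit will be used. If an unshown document defines control minus intervention, only a clarification is needed. But the article does state the rule, and nothing in it supports the reversed contrast. A sound sample size does not correct a decision sentence that conflicts with it.

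A reader might go further and infer that any amount of harm would pass. That needs the rule to mean lower limit above −0.25 for intervention minus control. On that reading the pass rate is about 100% at true worsenings of 0.25, 0.5 and 1.0. It fits the text less well, because the limit must lie within the margin of the control mean, and a lower limit of +1.0 does not.

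**Conclusion.** The point holds as an unsigned contrast and margin which, on the natural reading, test the wrong limit. Under that reading the chance of declaring non-inferiority at a true worsening of 0.25 is 95% instead of 5%, whatever rho is. At 0.5 it is about 10%, or about 2% to 20% for rho from 0.7 to 0.3. These figures use a normal approximation, the planning variance and 108 completers.

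The documents do not support saying that the trial will certainly apply the wrong test, or that the rule passes harm of any size. The sample size is sound and already fits the harm-side rule. Because the sentence decides the primary endpoint, it must be corrected before the data are analysed.

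**What to change.** Replace the decision sentence with: *Difference = (change in ACQ from period baseline during intervention) minus (change in ACQ from period baseline during control); positive values mean worse control under withdrawal. Non-inferiority is concluded if the upper limit of the one-sided 95% confidence interval is below +0.25 ACQ points.*

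This keeps the baseline correction that both statistical sections require; a plain difference of endpoint scores would change the primary endpoint. If an unshown document already defines control minus intervention, the equivalent is to state that contrast and require the lower limit to be above −0.25.

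The cost is one amended passage in the protocol and analysis plan before database lock. N stays at 120 and no further data are needed.

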## Discussion

Obesity is more and more present among all asthma endotypes, often associated with T2-low endotypes and therefore not responsive to steroids. Nevertheless, guidelines advocate the use of ICS in all asthma patients, regardless of T2-endotype. As a result, obese T2-low asthma patients potentially suffer from the side effects of high dosed ICS while remaining poorly controlled.

T2 low asthma can be classified as obesity-related asthma, paucigranulocytic asthma or neutrophilic asthma with overlap between phenotypes [3, 39]. With the obesity pandemic soaring, the prevalence of asthma in combination with obesity is increasing, resulting in poor outcomes, such as a high burden of disease, frequent exacerbations, and increased risk for hospitals admission [40–44]. In this group, approximately 75% of patients can be classified as uncontrolled [45]. In patients with evident type 2 inflammation, such as eosinophilic- or allergic disease, good asthma control is often achieved by treatment with corticosteroids. However, T2-low asthma differs substantially from T2-high asthma, as underlying pathways are steroid-resistant [46–50]. Still, GINA guidelines recommend escalating ICS dose in patients with poor asthma control, without considering the T2-endotype. This is potentially problematic in patients with T2-low asthma, as these patients typically suffer from a high disease burden, regardless of ICS dose. This may lead to high dosed ICS without substantial improvement of asthma control [51]. High dosed ICS subsequently increases the risk of side effects, such as weight gain, diabetes, and high blood pressure [52–54]. These side effects are unfavourable, particularly in patients with the common combination of T2-low asthma and obesity, as high dosed ICS may worsen obesity, subsequently leading to worse asthma control, creating a vicious circle. This hypothesis is supported by a recent trial that demonstrated that asthma control decreased after increasing the dose of ICS in patients with non-eosinophilic or neutrophilic sputum [45]. We postulate that the adverse effects of ICS do not outweigh the health benefits in these patients.

The STOP trial is the first to investigate ICS tapering and discontinuation in the population of patients with T2-low asthma and obesity. Several trials on ICS tapering have been published in the past decades [15–21, 51, 55, 56]. However, these trials did not differentiate between T2-high and T2-low asthma. This concludes that ICS cannot be tapered in a mixed population of T2-high and T2-low asthma. However, additional subgroup analysis found that patients with low eosinophil count were more likely to taper and/or discontinue ICS [18, 20, 55]. Later studies, such as Demarche et al., selected patients with low eosinophils and successfully tapering or discontinuing ICS in more than half of these patients. Those encouraging results demonstrated the importance of selection on low blood eosinophils. In addition, recent guidelines usually define the threshold of low blood eosinophils as < 150 cells/µL, whereas earlier trials used thresholds of < 300-400cells/µL. Thus, adhering to the most recent definition of low blood eosinophils may increase the percentage of success.

The primary safety issue regarding this trial consists of patients worsening due to ICS tapering. Based on earlier trials and literature, we estimate the risk of severe exacerbations in patients with obese T2-low asthma as very low in patients with T2-low asthma and obesity [15, 17, 56]. However, to meet safety standards, a detailed plan was created to handle these adverse events.

Current guidelines advocate the use of ICS in all asthma patients. The STOP trial investigates opportunities to taper ICS to zero in patients with obese T2 low asthma. Successful discontinuation of ICS will lead to decreased exposure to glucocorticosteroids. On the contrary, failed ICS tapering justifies exposure to glucocorticosteroids in this patients group, as benefits appear to outweigh risks. Either way, the outcomes of this trial are expected to influence future guidelines on T2 low asthma and obesity.

## Data Availability

Data for this study are not yet available. After completion of the STOP trial, raw data can be obtained upon reasonable request from the corresponding author.

## Abbreviations

ACQ: Asthma Control Questionnaire
AQLQ: Asthma Quality of Life Questionnaire
BMI: Body Mass Index
CCMO: Dutch, competent authority
CI: Confidence interval
COPD: Chronic obstructive pulmonary disease
CGG: Dutch, obesity clinic CGG
DSMB: Data Safety Monitoring Board
EDC: Electronic data capturing
eNose: Electronic nose
FeNO: Fractional exhaled nitric oxide
FEV1: Forced exhaled volume in 1 s
FSS: Fatigue Severity Scale
GCP: Good clinical practice
ICS: Inhaled CorticoSteroids
IMDH: Inosine monophosphate dehydrogenase
IQR: InterQuartile range
MRC: Medical Research Council
mTOR: Mechanistic target of rapamycin
NTR: Netherlands trial register
OCS: Oral CorticoSteroids
OSAS: Obstructive sleep apnea syndrome
PBMCs: Peripheral blood mononuclear cells
pMDI: Pressurized Metered-Dose inhaler
RCT: Randomized controlled trial
(S)AE: (Serious) adverse event
SD: Standard deviation
STOP: Steroid tapering in obese patients with type 2 low asthma
SUSAR: Suspected unexpected adverse reaction
T2-hidden: Type 2 hidden
T2-high: Type 2 high
T2-low: Type 2 low
WMO: Dutch, Medical Research Involving Human Subjects Act
